#### Relevant concomitant care permitted or prohibited during the trial {11d}

Patients will be prepared in accordance with cardiopulmonary bypass, and standard monitoring will be established, including electrocardiograph (ECG), non-invasive blood pressure (NIBP), pulse oxygen saturation (SpO_2_), body temperature (T), bispectral index (BIS), and cerebral oxygen, with an external automatic defibrillation patch attached. Radial artery and right internal jugular vein catheterization, under local anesthesia, will facilitate monitoring of invasive arteriovenous pressure. General anesthesia induction will involve midazolam (0.03 ~ 0.08 mg/kg), etomidate (0.2 ~ 0.6 mg/kg), rocuronium (0.6 ~ 0.9 mg/kg), and sufentanil (0.3 ~ 0.4 μg/kg). Tracheal tubes will be inserted when the BIS value decreased to 40 ~ 50, initiating mechanical ventilation with a tidal volume of 6 to 8 mL/kg, respiratory rate of 12 to 15/min, and a 1:1 air-oxygen mixture, maintaining ETCO_2_ between 35 and 45 mmHg.

The anesthesia will be maintained with propofol (4 ~ 6 mg/kg/h), remifentanil (0.08 ~ 0.3 µg/kg/min), and sevoflurane (1 ~ 2 vol%). Heart rate and mean arterial pressure will be maintained within ± 20% of baseline, except during rapid ventricular pacing. Blood potassium level will be maintained between 4.5 and 5.5 mmol/L and BIS will be kept between 40 and 60 throughout operation.

Patients will be delivered to cardiac surgery intensive care unit postoperatively for standardized monitoring and management. A postoperative patient-controlled intravenous analgesia (PCIA) regimen will be established as part of a multimodal pain regimen, with sufentanil (2.5 µg/mL, limit dose 200 µg) combined with dexmedetomidine (3 µg/mL, limit dose 200 µg) and tropisetron 5 mg. The PCIA pump will be programmed for a 2 mL bolus with a lockout interval of 15 min and a basal infusion of 4 mL/h. Rescue analgesia will include paracetamol and tramadol hydrochloride tablets (one tablet, p.o) for VAS > 4 at rest, and 1 mg of hydromorphone intravenously for severe pain (VAS > 7). Patients will be educated on PCIA pump usage.

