### Outcomes {12}

#### Primary and secondary outcomes

The primary outcome will assess the quality of recovery at 24 h and 48 h, measured using the QoR-40 scale [11, 13].

The secondary outcomes include:VAS pain scores: assessment at rest and during coughing at 6 h, 12 h, 24 h, and 48 h post-surgery [9]Frequency of PCA utilization: evaluation at 24 h and 48 h following surgery [14, 15]Opioid consumption: quantification at 24 h and 48 h post-surgery [14, 15]Time and frequency of rescue analgesia and severe pain: analysis at 24 h and 48 h after surgery [16]Incidence of nausea and vomiting: determination at 48 h post-surgery, along with the dosage of antiemetic drugs [15]

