### Statistical methods

#### Statistical methods for primary and secondary outcomes {20a}

All normally distributed continuous variables will be expressed as mean ± standard deviation and analyzed with Student’s *t*-test. For non-normal distributed data, the Mann–Whitney *U* test will be used, and results will be presented as median and interquartile interval. Categorical variables will be described with frequencies (%) and compared using the chi-square test or Fisher’s exact test. A 95% confidence interval (CI) for differences in means (for continuous outcomes) or relative risks (for categorical outcomes) will be calculated. A *P* value < 0.05 will be considered statistically significant. Statistical analyses will be performed using SPSS software version 26 (IBM, New York, USA).

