## Discussion

This single-center, randomized controlled trial aims to investigate the effect of ultrasound-guided SAPB on the early recovery quality and analgesic of patients undergoing transapical TAVI surgery.

Transapical TAVI, a minimally invasive surgical method for aortic valve lesions, offers a promising alternative for elderly and high-risk patients who may not be suitable candidates for traditional surgery. As evidence-based medicine continues to evolve, the indications for TAVI are expanding globally, leading to increased surgical volume and a gradual extension of indications to younger, lower risk, and longer life expectancy groups [17, 18]. However, perioperative analgesia and postoperative recovery of this minimally invasive cardiac surgery have not received widespread attention.

As evidence-based medicine continues to evolve, optimizing postoperative pain management becomes increasingly crucial. A comprehensive and individualized analgesia and rehabilitation program are vital. Perioperative multimodal analgesia, particularly regional block-based approaches, plays a pivotal role in promoting rehabilitation. SAPB is a fascial plane block with minimal impact on peripheral blood vessels and presents a safer and more maneuverable alternative without sympathetic block [19]. To address the gaps in evidence regarding SAPB’s effectiveness in acute regional analgesia following minimally invasive cardiac surgery, this trial evaluates the analgesic effect of SAPB in transapical TAVI using measures such as opioid consumption, analgesic pump pressing times, VAS pain scores at rest and during coughing, and remedial analgesia time. In terms of procedure, ultrasound-guided SAPB requires specialized training and expertise. Ensuring that the researchers performing this procedure are proficient in this technique is crucial for maintaining consistency and accuracy in drug administration. Therefore, establishing ongoing training and certification processes is essential to address this issue. In our current recruitment data, no complications such as bleeding or hematoma have been observed, indicating that SAPB can be safely used in TAVI patients undergoing intraoperative heparinization.

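### Time of rescue analgesia is right-censored at 48 h, but the stated methods for continuous variables give no rule for patients who are never rescued

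*Protocol article*

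**What the plan says.** All places are in the protocol article.

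- **Outcomes {12}** lists among the secondary outcomes "Time and frequency of rescue analgesia and severe pain: analysis at 24 h and 48 h after surgery". The Discussion names time of rescue again among its measures of the block's analgesic effect: "VAS pain scores at rest and during coughing, and remedial analgesia time".
- **Concomitant care {11d}** makes rescue conditional. It is triggered by a resting VAS above 4, with a separate drug for severe pain, defined as VAS above 7. All patients also have a patient-controlled pump with a basal infusion.
- **Statistical methods {20a}**, which covers primary and secondary outcomes, gives three rules. For normal data: "All normally distributed continuous variables will be expressed as mean ± standard deviation and analyzed with Student’s" *t*-test. Otherwise: "For non-normal distributed data, the Mann–Whitney *U* test will be used". For categories: "Categorical variables will be described with frequencies (%) and compared using the chi-square test or Fisher’s exact test". The effect measures are a difference in means or a relative risk, with 95% confidence intervals.
- **Missing data {20c}** names multiple imputation and nothing else.
- **Table 1** marks rescue analgesia at 24 h and 48 h, but severe pain at 48 h only.

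No section names a censoring rule, a time-to-event method, a time origin for the rescue time, or a score for patients who are never rescued.

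**The concern.** A time is a continuous variable, so under {20a} the time of rescue goes to a *t*-test or Mann–Whitney test. Those tests need a value for every patient, and a patient not rescued by 48 h has none. The analyst must then leave such patients out, assign them a value or impute one, and the article does not say which.

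The easiest course in a standard package is to leave the cell blank, so that only rescued patients are compared. That group is formed after randomisation by an event the block is meant to prevent. Patients whom the block spared rescue drop out of the comparison, and a real delay or avoidance of rescue can appear as no difference. Multiple imputation does not help. The value is not missing, because the event did not happen, and imputing from rescued patients would give rescue times to patients who were never rescued.

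Left open, the choice could be made after the data are seen, and the result depends heavily on it.

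**Working it through.** **The plan's own figure.** The Sample size section uses means of 167 and 184 (difference 17), SD 23, two-sided alpha 0.05, power 80% and 10% dropout.

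- n = 2 × (1.96 + 0.842)² × 23² / 17² = 2 × 7.85 × 529 / 289 = 28.7, so 29 per group.
- 29 / 0.9 = 32.2, so 33 per group, as stated; 35 are planned.

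This is sized on QoR-40 and does not depend on the rescue outcome.

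**Inputs for the check.** From the article: 35 per arm, 48 h follow-up, two-sided 0.05. Assumed, because the article gives no rescue rates: 48 h rescue proportions p, varied from 40% vs 15% to 90% vs 60% (control vs block).

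**Model 1, constant hazards.** λ = −ln(1 − p) / 48. The hazard ratio is ln(1 − p_block) / ln(1 − p_control). For 60% vs 30% it is 0.357 / 0.916 = 0.39, with 35 × (0.60 + 0.30) = 31.5 rescued patients expected.

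Mean time among the rescued is 1/λ − 48(1 − p)/p:

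- control: 48 / 0.916 − 48 × 0.4 / 0.6 = 52.4 − 32.0 = 20.4 h;
- block: 48 / 0.357 − 48 × 0.7 / 0.3 = 134.6 − 112.0 = 22.6 h.

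So halving the proportion rescued moves the mean among rescued patients by only about 2 h.

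Simulated power, 2,500 trials per row (standard error at most √(0.25 / 2500) = 0.01):

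| Rescued by 48 h | Hazard ratio | *t*, rescued only | Mann–Whitney, rescued only | Mann–Whitney, all, never-rescued tied at 48 h | Log-rank, all | Fisher, rescued yes/no |
|---|---|---|---|---|---|---|
| 40% vs 15% | 0.32 | 0.05 | 0.04 | 0.67 | 0.68 | 0.58 |
| 50% vs 20% | 0.32 | 0.06 | 0.05 | 0.76 | 0.77 | 0.68 |
| 60% vs 30% | 0.39 | 0.06 | 0.06 | 0.73 | 0.76 | 0.65 |
| 70% vs 35% | 0.36 | 0.09 | 0.08 | 0.84 | 0.86 | 0.77 |
| 80% vs 50% | 0.43 | 0.13 | 0.12 | 0.76 | 0.81 | 0.69 |
| 90% vs 60% | 0.40 | 0.28 | 0.26 | 0.89 | 0.92 | 0.79 |

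Cross-check of the 60% vs 30% row by Schoenfeld's formula: (√31.5 / 2) × |ln 0.389| − 1.96 = 2.806 × 0.944 − 1.96 = 0.69, which gives power 0.75 against 0.76 simulated. With 30% in both arms the five tests reject in 0.056, 0.044, 0.049, 0.049 and 0.031 of trials. A repeat of the simulation gave 4–26% for rescued-only tests, 66–92% for log-rank, 66–87% for all-patient Mann–Whitney and 57–78% for Fisher.

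**Model 2, the block changes only the share rescued, not the timing among the rescued.** Over the same rates, power is 0.04–0.06 for rescued-only tests, 0.64–0.85 for log-rank, 0.58–0.80 for all-patient Mann–Whitney and 0.55–0.79 for Fisher.

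**Severe pain.** Outcomes {12} analyses it at 24 h and 48 h. Table 1 marks it at 48 h only, while the rescue row is marked at both times.

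**The case against.** The strongest reply has four parts.

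1. *The stated methods are wider than the two tests for continuous data.* The outcome is time and frequency, and chi-square or Fisher's exact test with a relative risk fits the frequency half. A reader might infer that the plan has no usable method for rescue. It does have one, with power of about 55–79% under the assumed rates. This stands.
2. *The article never says that unrescued patients are dropped.* A reader might infer this from the choice of tests, but the text is silent. Mann–Whitney can keep everyone by ranking the never-rescued last, and under proportional hazards it then comes close to log-rank. This stands too: the low power belongs to a rescued-only comparison, not to the named tests as such.
3. *Censoring rules for a secondary outcome are commonly left to the analysis plan, which is not shown.* This holds for the detail. But {20a} does more than stay silent: it assigns continuous variables a test and a difference in means, and that assignment does not fit a censored time without a further rule.
4. *The severe-pain mismatch is small.* VAS is scheduled at 24 h and severe pain is defined by VAS, so severe pain at that visit can be derived. That is true, but the two places still disagree.

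A reader might also infer that the trial would miss the effect it seeks. The article does not support that. The primary outcome is QoR-40, and analgesia is also measured by VAS, pump use, opioid consumption and rescue frequency.

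**Conclusion.** The point holds in a limited form. Time of rescue analgesia is right-censored for patients not rescued by 48 h. The rule for continuous variables does not say how to treat them, and multiple imputation is not an answer.

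The size depends on a choice that the article leaves open. At 60% vs 30%, the same Mann–Whitney test has power 0.06 among rescued patients and 0.73 when all patients are kept. The rescue rates are assumptions. The contrast holds across the whole range tried and under both models, though rescued-only power does rise, to 0.26–0.28, at 90% vs 60% with constant hazards.

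This affects one half of one secondary outcome. It does not touch the primary outcome, the sample size or the comparison of rescue frequency. It should be settled before the data are analysed, but it does not threaten the trial's main conclusion.

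**What to change.** - Define the outcome as time from end of surgery to first rescue analgesia, in all randomised patients, censored at 48 h if no rescue has been given.
- Analyse it by Kaplan–Meier with a log-rank test and a Cox hazard ratio. Mann–Whitney on all patients, with the never-rescued ranked last, is an acceptable alternative if stated in advance. Log-rank is the safer choice, since it lost less power under Model 2 (at 90% vs 60%, 0.78 against 0.58).
- State that patients without rescue are not missing for this outcome, so that multiple imputation is not applied to them.
- Keep the proportions rescued by 24 h and 48 h, with relative risks, under the categorical methods already stated.
- Apply the time-to-event analysis to severe pain only if its onset is time-stamped between the scheduled VAS assessments (6, 12, 24 and 48 h). Otherwise onset is known only to lie between visits, and the proportions suffice.
- Reconcile Outcomes {12} and Table 1 on whether severe pain is assessed at 24 h.

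The cost is a few sentences of analysis wording and one table entry. It needs no extra patients or visits, and time of rescue is already an outcome.

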### Participant timeline {13}

The schedule of enrollment, interventions, and assessments is shown in Table 1.

**Table 1 Tab1:** Participant timeline

	**Enrolment**	**Allocation**	**Post-allocation**			
Timepoint	** − 1 day**	**Surgery day**	**6 h after surgery**	**12 h after surgery**	**24 h after surgery**	**48 h after surgery**
Enrollment						
*Eligibility screen*	X					
*Informed consent*	X					
Allocation		X				
Interventions						
*SAPB group*		X				
*Control group*		X				
Assessments						
*QOR-40*	X				X	X
*VAS pain scores*			X	X	X	X
*Times of PCA*					X	X
*Opioid consumption*					X	X
*Rescue analgesia*					X	X
*Severe pain*						X
*Nausea*						X
*Vomit*						X
*Dosage of antiemetic drugs*						X

*SAPB*, serratus anterior plane block; *QOR-40*, Quality of Recovery-40 scale; *PCA*, patient-controlled analgesia

### Sample size {14}

The sample size calculation is based on the primary outcome. According to a prior publication, where mean of group 1 was 167 and the mean of group 2 was 184, with known group standard deviations of 23 [13], a sample size of 33 for each group (66 in total) will be required to achieve a power of 80% to detect the difference at a two-side *α* level of 0.05, taking into account a dropout rate of 10%. Ultimately, we plan to include 35 participants in each group.

### Recruitment {15}

Patients will be provided with comprehensive information about the research procedures, including potential risks, the benefits, and postoperative follow-up, during pre-anesthesia clinic consultations to ensure thorough understanding and enhance patient compliance. Recruitment will be conducted at the Second Affiliated Hospital of Army Medical University, PLA. The recruitment for this study began on February 28, 2023. Our hospital currently performs 3–4 transapical TAVI procedures per month and has recruited 50 participants to date. To minimize the risk of not reaching the recruitment target, we expect to complete recruitment by January 2025.

### Assignment of interventions: allocation

#### Sequence generation {16a}

Eligible patients will be randomly allocated to either the ultrasound-guided SAPB group or the control group at a 1:1 allocation ratio after providing written informed consent. The randomization sequence will be generated by an independent researcher using SPSS software version 26.0 (IBM, New York, USA).

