### Eligibility criteria {10}

#### Inclusion criteria

Patients will undergo a face-to-face screening 1 day prior to surgery based on the following eligibility criteria:Adult patients aged40–70 yearsASA II ~ IV classificationPatients planning to undergo transapical TAVI under general anesthesiaPatients expressing willingness to participate in this study and signed informed consent

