#### Exclusion criteria

Patients meeting any of the following criteria will be excluded from the study:Allergy to LAsHistory of mental illness or taking psychotropic drugsSevere abnormalities in coagulation functionLong-term use of analgesics or sedativesHistory of drug abuse, alcohol, or opioid abuseRecent acute pain or chronic painPostoperative mechanical ventilation ≥ 24 hDecline to participate in the studyParticipants retain the right to withdraw from the study at their discretion for any reason or if researchers determine their inclusion is inappropriate

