#### Intervention description {11a}

Ultrasound-guided SAPB will be conducted after induction of general anesthesia. Patient will be positioned supine with the upper limb abducted, and the ultrasonic probe will be located in the 5th intercostal space along the left axillary line. The probe’s direction will be adjusted to identify the tissue structures such as latissimus dorsi, pectoralis major, pectoralis minor, and serratus anterior. Using an in-plane technique, a 22-G nerve block needle will be advanced to the surface of the serratus anterior muscle and aspirated to ensure no blood and gas. Subsequently, 2 mL of local anesthetic mixture (0.4% ropivacaine + 10 mg dexamethasone) will be slowly injected. The injection will be performed while observing the spread of the anesthetic between the fascia layers, as indicated by a hypoechoic area on ultrasound, and additional mixture will be slowly injected. The control group will be given 40 mL normal saline.

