#### Implementation {16c}

As soon as the patients enters the operation room, the attending anesthesiologist will open the corresponding numbered envelope, verify the patient’s allocation, and proceed to implement the corresponding anesthesia plan accordingly.

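### An exclusion criterion that can be met only about 24 h after surgery removes patients who have already been randomised and treated

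*Protocol article*

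**What the plan says.** The relevant statements in the protocol article, in the order in which the events occur:

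- **Screening.** Inclusion criteria: "Patients will undergo a face-to-face screening 1 day prior to surgery based on the following eligibility criteria". Table 1 also places the eligibility screen at day −1.
- **Exclusion.** Exclusion criteria: "Patients meeting any of the following criteria will be excluded from the study". One listed item is mechanical ventilation for 24 h or more after the operation.
- **Randomisation.** Sequence generation {16a}: "Eligible patients will be randomly allocated to either the ultrasound-guided SAPB group or the control group at a 1:1 allocation ratio", after written consent.
- **Allocation revealed.** Implementation {16c}: when the patient enters the operating room, "the attending anesthesiologist will open the corresponding numbered envelope, verify the patient’s allocation".
- **Treatment.** Intervention description {11a}: "Ultrasound-guided SAPB will be conducted after induction of general anesthesia". The control group receives saline.
- **Primary outcome.** Primary and secondary outcomes: "The primary outcome will assess the quality of recovery at 24 h and 48 h, measured using the QoR-40 scale".

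The section on non-adherence and missing data {20c} provides multiple imputation if data are missing. It does not say whether this covers patients excluded under the ventilation item.

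**The concern.** An eligibility criterion should be decidable before allocation. This one is decided by what happens to the patient after the block or saline has been given. Long ventilation is plausibly a marker of poor early recovery, which is what the QoR-40 is meant to capture. The Background section {6a} expects the block to lower opioid use and its adverse effects and to help recovery, so by the trial's own rationale the treatment may change who is still ventilated at 24 h.

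Selecting patients on such a variable gives up the protection of randomisation. The rule works mechanically, so blinding of patients and assessors does not prevent the problem. Even where no bias arises, the result would describe only patients who recovered fast enough to be off the ventilator within a day.

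**Working it through.** **1. Order of events.** Screening (day −1), then allocation revealed (entry to the operating room), then block or saline (after induction), then surgery, then the ventilation item becomes decidable (about 24 h after surgery), which is also when the first primary QoR-40 is due. The item cannot be applied at any step before treatment. Its stated consequence is exclusion from the study, so it can act only on randomised and treated patients.

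**2. The plan's own sample size.** Inputs from Sample size {14}: means 167 and 184 (difference 17), SD 23, two-sided α 0.05, power 80%, dropout 10%.

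- n per group = 2 × (1.96 + 0.842)² × 23² / 17² = 28.7, rounded up to 29.
- 29 / (1 − 0.10) = 32.2, rounded up to 33.

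The stated 33 per group reproduces, and 35 are planned.

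**3. Effect on power.** The documents give no ventilation rate, so the removal rates are assumptions. Normal-approximation power for a difference of 17:

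| Removed in each arm | Left per arm | Power |
|---|---|---|
| 0% | 35 | 87% |
| 5% | 33.3 | 85% |
| 10% | 31.5 | 83% |
| 15% | 29.8 | 81% |
| 20% | 28 | 79% |

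Power is not the problem.

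**4. Bias, extreme illustration.** Assume no true effect on QoR-40, normal scores with SD 23, and that the removed patients are exactly the lowest scorers. Removing the lowest fraction p raises the arm mean by 23 × φ(z_p) / (1 − p).

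- p = 0.10: 23 × 0.1755 / 0.90 = 4.48 points.
- p = 0.03: 23 × 0.0680 / 0.97 = 1.61 points.
- 10% against 0%: shift 4.48, which is 26% of 17.
- 10% against 3%: shift 4.48 − 1.61 = 2.87, which is 17% of 17.

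Standard error = 23 × √(1/n₁ + 1/n₂), with 35 per arm less those removed and the SD kept at 23:

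- 10% against 0%: 23 × √(1/31.5 + 1/35) = 5.65; shift/SE = 0.79; two-sided rejection rate at 1.96 = 12.5%.
- 10% against 3%: 23 × √(1/31.5 + 1/33.95) = 5.69; shift/SE = 0.50; rejection rate = 8.0%.

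If ventilation is correlated only 0.5 with QoR-40, the shifts halve to 2.24 and 1.44 points and the rejection rates fall to 6.8% and 5.7%.

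**5. Direction, with a different set of assumptions.** Let D be how much lower the removed patients score than the retained ones. With no true effect, each arm's retained mean exceeds its full mean by r × D, where r is the fraction removed. The shift (SAPB minus control) is (r_SAPB − r_control) × D. For D = 23 to 46 points:

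- SAPB 5%, control 10%: −1.15 to −2.3.
- SAPB 5%, control 15%: −2.3 to −4.6.
- Equal rates: 0.

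If the block shortens ventilation, more control patients are removed, the control mean is flattered, and the bias runs against SAPB.

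**The case against.** The strongest reply is that the effect may be small or absent. No rate of long ventilation is given. If the block does not affect ventilation, removal is equal in expectation and there is no bias under no true effect. The 8–12.5% rejection rates need a large effect on ventilation with none on QoR-40, and near-perfect overlap between ventilated patients and lowest scorers; 10% of 35 is only 3 or 4 patients. All of this stands, and it limits the size that can be claimed. It does not rescue a criterion that cannot be assessed before treatment.

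A reader might infer three stronger points that the documents do not support.

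- *That the rule inflates false claims for SAPB.* The only mechanism the article offers, a block that improves recovery, pushes the bias the other way; most excess rejections would then favour control.
- *That the exclusion rule and the imputation rule contradict each other.* The article says only that missing data will be imputed. Whether an excluded patient counts as missing is not stated, so a contradiction would be an inference.
- *That the plan is at fault for naming no analysis set.* An article commonly leaves that to a fuller document. The fair target is the rule that the article does state.

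**Conclusion.** The concern holds as a wrongly placed rule. The article lists, as a ground for exclusion from the study, an event that can occur only after randomisation and treatment and that is plausibly tied to the primary outcome. Applied as written, it breaks the randomised comparison and restricts the result to faster recoverers.

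Neither the size nor the presence of bias can be established from the documents. The range runs from zero (equal removal, no true effect) to about 4.5 points in the extreme scenario, and 1.4–2.2 points with a correlation of 0.5. These figures rest on assumed removal rates and on the SD of 23 in the sample size section. That the patients leave the analysis, and not only follow-up, is the natural reading of the exclusion sentence, but the article does not spell it out.

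**What to change.** 1. Remove long postoperative ventilation from the exclusion criteria, so that every criterion can be assessed before the envelope is opened.
2. Analyse all randomised patients in their allocated arm. Recruitment {15} reports 50 already enrolled; include any of these who were removed under the rule, where their data exist.
3. Before unblinding, state one primary-analysis rule for patients who cannot complete the 24 h QoR-40 because they are still ventilated, for example a worst rank, instead of letting them fall by default to the imputation in {20c}. Deleting the criterion without this step would leave a gap at a primary time point. Use the 48 h score where it was obtained.
4. Report the number ventilated for 24 h or more by arm, and keep the analysis without these patients as a sensitivity analysis.

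The cost is a short amendment and some analysis wording, with no extra patients or procedures. A few low or non-evaluable scores will enter the primary analysis and may widen the interval slightly. Whether 48 h scores were collected for anyone already removed is not known from the article, so full recovery of those patients cannot be promised.
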